#### Criteria for the premature termination of the trial

The criteria for stopping the trial will be if a patient dies from an RTX treatment-related infection, or if two patients experience the same serious unsuspected serious adverse reaction (SUSAR) which has severe or life-threatening consequences.

### Safety reporting

We do not aim to collect adverse events such as minor trauma (scratches, cuts) in patients who are otherwise well. Adverse events will otherwise be classified according to whether they are:Infections (minor: self-limiting infection such as the common cold; modest: non-self-limiting where an antibiotic is prescribed but the clinical course and recovery is not related to the underlying condition and its treatment; or severe: where antibiotic therapy ± other therapy is required with the infection related to drug effects on immune function).Immune function-related such as neutropaenia.Related to the skin, for example, rashes.Related to the musculoskeletal system, such as joint pain.Related to gastrointestinal upset.Related to hepatic function.Others.

The trial will be stopped if a patient dies from an RTX treatment-related infection or if two patients experience the same SUSAR which has severe or life-threatening consequences.

According to section 4.6 of the summary of product characteristics (SmPC) (Mabthera [the product name for RTX] 100 mg and 500 mg concentrate for solution for infusion), RTX should not be administered to pregnant women. The SmPC states that ‘Rituximab should not be administered to pregnant women unless the possible benefit outweighs the potential risk’. Due to the long retention time of RTX in B cell-depleted patients, women of childbearing potential need to use effective contraceptive methods during treatment and for 12 months following RTX therapy (in line with the SmPC for RTX). If a female participant becomes pregnant within 12 months of taking the RTX drug, the details of the pregnancy need to be reported to the chief investigator, trial manager and sponsor within 24 hours of the site learning of its occurrence on the pregnancy reporting form.

If a patient or their partner (where the participant is male) becomes pregnant, within 12 months of taking RTX, the pregnancy must be reported as per the trial-specific guidance document for pregnancy reporting and followed up to completion of pregnancy.

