RTX has an excellent safety record in the young and has been used extensively in paediatric practice to treat autoimmune cytopaenias, juvenile dermatomyositis, juvenile idiopathic arthritis, SLE and renal disorders, with significant side effects uncommon.^16 34^ Rates of infection appear to be low.^14^ Hypogammaglobulinaemia is a possible but very rare side effect in young people and may reflect an underlying but previously unrecognised immunodeficiency.^35^ The rare complication, progressive multifocal leucoencephalopathy, has been seen almost exclusively in adult patients with complex disorders who have received multiple immune suppressants (eg, those with B cell malignancies, multiorgan refractory SLE).

The aim of this clinical trial is to explore whether RTX administration will have a beneficial impact on the disease course in young people presenting with Graves’ hyperthyroidism. Specifically, we have set out to establish whether a single 500 mg dose of RTX, when administered together with a 12-month course of ATD, will increase remission rates in young people with Graves’ hyperthyroidism.

Previous treatment regimens in adults with Graves’ disease or GO have typically used between 1000 and 2000 mg RTX administered in divided doses. In contrast, a single dose of 500 mg RTX was used in a recent trial of patients with GO.^30^ The investigators in this trial subsequently reduced the dose of RTX to 100 mg in some of their trial patients because complete peripheral B cell depletion was still seen with this smaller dose. Our selection of 500 mg of RTX was a pragmatic decision bearing in mind the established efficacy in many disorders of 2×1000 mg doses versus the observation that a profound effect on B cell numbers was still observed with a much smaller dose. We were also keen to reduce the complexity associated with repeated visits to hospital for an intravenous infusion. By using a modest dose of 500 mg RTX on one occasion, we anticipated a meaningful effect on immune system function but a reduction in potential side effects.^27^

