#### Secondary

TRAb titre and related thyroid hormone status at the time of RTX administration and 2 years post-RTX.Time to recovery of B cell lymphocyte numbers in peripheral blood to the normal local lab reference range in relation to thyroid hormone status.Cumulative dose of ATD (mg/kg) in relation to thyroid hormone status 2 years post-RTX.Time taken for TSH and thyroid hormone concentrations to normalise to within the local laboratory reference range post-RTX, and describe biochemical thyroid status in the period between cessation of ATD and 2 years post-RTX in each patient.The frequency and nature of adverse events.

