### Visit details and assessments

Following screening and consent, RTX is administered at the baseline visit (week 0). Subsequent visits are scheduled until 24 months; the details are provided in table 2. In addition, after each visit in the first 12 months, participants are contacted by telephone to document changes in ATD dosages. Calls should be completed within 10 days of the visit.

**Table 2 T2:** Schedule of events

Assessments/Intervention	Trial period														
	Screening/Consent	Trial intervention	Follow-up												
	Week −6 to 0	0	4	8	12	16	20	28	36	44	52	65	78	91	104
Confirmation of eligibility	X	X													
Informed consent and assent	X														
HBsAg, HB Core and HCV antibodies	X														
Pregnancy test (women)	X	X									X				
Medical history		X													
Clinical examination		X	X	X	X	X	X	X	X	X	X	X	X	X	X
Height		X						X			X		X		X
Weight		X	X	X	X	X	X	X	X	X	X	X	X	X	X
RTX infusion		X													
ATD regimen		X	X	X	X	X	X	X	X	X	X				
ATD compliance			X	X	X	X	X	X	X	X	X				
Concomitant medication		X	X	X	X	X	X	X	X	X	X	X	X	X	X
Adverse and serious adverse event		X	X	X	X	X	X	X	X	X	X	X	X	X	X
Thyroid function (TSH, FT4 and FT3)		X	X	X	X	X	X	X	X	X	X	X	X	X	X
Liver function (ALT and bilirubin) if on PTU		X	X	X	X	X	X	X	X	X	X	X	X	X	X
Thyroid antibodies (TRAB and TPO)		X			X			X	X		X				X
Lymphocyte subsets*		X	X		X			X	X		X				X
Full blood count		X	X		X			X	X		X				X
Immunoglobulin levels (IgG, IgM, IgA)		X			X			X	X		X				X
Specific antibody levels (tetanus, Hib, pneumococcus)		X									X				X
Thyroid function (TSH, FT4 and FT3)—central analysis		X									X				X
Serum for exploratory analyses		X									X				X

ATD dose is adjusted at each visit if required.

*Lymphocyte subsets: T cells (CD3), helper T cells (CD4), cytotoxic T cells (CD8), B cells (CD19) and class switch B cells (CD27+ IgD−).

ALT, alanine transaminase; ATD, antithyroid drug; FT3, free tri-iodothyronine; FT4, free thyroxine; HB Core, hepatitis ‘B’ Core antibody; HBsAg, hepatitis ‘B’ surface antigen; HCV, hepatitis ‘C’ virus antibody; Hib, haemophilus influenzae type B; PTU, propylthiouracil; RTX, rituximab; TPO, thyroid peroxidase; TRAb, thyrotropin receptor antibody; TSH, thyroid stimulating hormone.

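### The infection scale in Safety reporting separates 'modest' from 'severe' by relatedness to treatment rather than by clinical severity, and leaves some infections without a grade

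*Protocol article*

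**What the plan says.** The Safety reporting section of the protocol article lists the classes into which adverse events will be sorted. Infections come first and are the only class with sub-grades:

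- lowest grade: "minor: self-limiting infection such as the common cold"
- middle grade: "modest: non-self-limiting where an antibiotic is prescribed but the clinical course and recovery is not related to the underlying condition and its treatment"
- top grade: "severe: where antibiotic therapy ± other therapy is required with the infection related to drug effects on immune function"

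The classification serves the last item in the list of secondary outcomes, "The frequency and nature of adverse events", which corresponds to secondary objective 5 on safety. Under Trial design the study is described as open-label and single-arm. The Discussion singles out infections among the possible adverse events.

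Two other provisions bear on the point. The schedule of events (Table 2) has a row "Adverse and serious adverse event", marked at week 0 and at every follow-up visit. The stopping rule, given under the criteria for premature termination and again under Safety reporting, reads in part: "The trial will be stopped if a patient dies from an RTX treatment-related infection or if two patients experience the same SUSAR".

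**The concern.** Minor, modest and severe look like steps on one scale of intensity. The first step does concern the nature of the infection: whether it resolves by itself. The second does not. Both upper grades involve an antibiotic, and what divides them is whether the infection or its course is attributed to treatment. No grade mentions hospital admission, organ support or threat to life.

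A reader of the results would take a count of 'severe' infections as a count of bad infections. Under this wording it is a count of antibiotic-treated infections that investigators, who know that every patient received rituximab, attributed to drug effects. There is no control arm against which to judge that attribution. Infection is the adverse event the authors themselves highlight, so this table is one that planners of a phase III trial are likely to consult.

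**Working it through.** No arithmetic in the article is at issue, and there is no stated figure to reproduce. The check is to apply the three definitions as rules.

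**Rules taken from Safety reporting**

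- Minor: self-limiting.
- Modest: not self-limiting, antibiotic prescribed, course and recovery not related to the disease and its treatment.
- Severe: antibiotic required (with or without other therapy), infection related to drug effects on immune function.

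For simplicity, 'related' stands here for both relatedness conditions. The consequence of that simplification is taken up below.

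| Self-limiting | Antibiotic | Judged related | Grade as written |
|---|---|---|---|
| yes | yes | yes | minor and severe |
| yes | yes | no | minor |
| yes | no | yes | minor |
| yes | no | no | minor |
| no | yes | yes | severe |
| no | yes | no | modest |
| no | no | yes | none |
| no | no | no | none |

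Adding a fourth attribute, life-threatening or not, doubles the table to 2 × 8 = 16 combinations. The grade is the same within all 8 pairs, because no definition refers to danger. Of the 16 combinations, 2 × 2 = 4 have no grade and 1 × 2 = 2 have two grades. These are counts of logical cases, not expected frequencies. Some combinations, such as self-limiting and life-threatening, will hardly occur.

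**What follows**

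1. Rows 5 and 6 differ only in the relatedness judgement, and that alone moves the infection between 'severe' and 'modest'. A serious infection with a course judged unrelated is 'modest'. A mild one judged related is 'severe'.
2. Rows 7 and 8 have no grade. A viral infection that does not resolve by itself and is treated only with an antiviral is an example.
3. Row 1 meets two definitions, because the top grade does not exclude self-limiting infections.

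**The two relatedness conditions are not opposites.** The middle grade asks whether the course and recovery are related to the underlying condition and its treatment. The top grade asks whether the infection is related to drug effects. An antibiotic-treated, non-self-limiting infection whose course is linked to the disease but not to a drug fits neither.

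**The drug is not named.** The ATD therapy section describes neutropaenia on carbimazole. An infection during that neutropaenia and one attributed to B cell depletion by rituximab would share the top grade, with nothing in the grade to tell them apart.

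**The case against.** The strongest reply is that little depends on these labels. Serious adverse events are checked at every visit from week 0, so a septic patient in intensive care is recorded as serious whatever the label. Identifying a SUSAR requires seriousness and relatedness to be judged event by event. The stopping rule refers to death from infection and to repeated SUSARs. It does use the word severe, but of a reaction's consequences, not of this infection grade. All of this stands. A reader might infer that dangerous infections would be hidden from the Data Monitoring Committee or could slip past the stopping rule. The article does not support that, and nowhere says that the committee sees only these grades.

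A reader might also infer that severity and causality are lost for good. They are not: for antibiotic-treated, non-self-limiting infections the label itself carries attribution, and severity can be restored where event descriptions are adequate.

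The wording leaves some room. The middle grade concerns course and recovery, so a life-threatening illness in a B-cell-depleted patient may well be judged related and escape 'modest'. The result therefore holds only where the investigator judges the course unrelated. The ungraded cases arise only where no antibiotic is given. Empirical antibiotic cover, or reading 'antibiotic' as any antimicrobial, would narrow that gap. Neither reading removes the mixing of severity with causality.

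Some examples that come to mind are weak. Hepatitis B/C infection is an exclusion criterion, and negative status must be confirmed before the infusion. On progressive multifocal leucoencephalopathy the Introduction says: "The rare complication, progressive multifocal leucoencephalopathy, has been seen almost exclusively in adult patients with complex disorders". The gap does not depend on either. The Discussion also says that the literature does not point to significant problems in otherwise healthy patients after one or two doses. That bears on how often the scale will matter, not on whether it is well defined.

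Finally, the article condenses a full protocol that may hold separate intensity and causality fields. Their absence here is not the point. The point is that the scale the article does state is built wrongly.

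**Conclusion.** The concern holds as a defect in a stated definition. The minor/modest/severe scale mixes severity with causality, and it is neither exhaustive nor mutually exclusive.

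Its reach is limited to the descriptive infection table within the adverse-event secondary outcome. There the 'severe' count would reflect investigators' attribution rather than intensity. The primary endpoint, the recording of serious adverse events and the stopping rule are unaffected.

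The effect cannot be sized from the document. A reader might put it as one or two of 27 patients, 1/27 = 3.7% or 2/27 = 7.4% on a severe-infection rate. The article defines no such rate as an endpoint, and the number of events that would change grade is unknown, so those figures do not measure the error.

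The verdict assumes a literal reading of the three definitions and, for the ungraded infections, that no antibiotic is given. Confidence is high on the wording. The practical consequence is modest, but the correction is cheap and worth making.

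**What to change.** In Safety reporting, replace the three infection grades with a standard toxicity scale based on clinical consequence (for example: no treatment; oral treatment; intravenous treatment or hospital admission; life-threatening; fatal), applied whatever the organism or type of antimicrobial. Record relatedness to rituximab and relatedness to antithyroid drug as two separate fields, or use those fields if the full protocol already has them. Regrade infections already recorded where their descriptions allow, and state how many could not be regraded. Report infections as a table of severity against relatedness.

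The cost is a small change to the adverse event form and the reporting table, plus the regrading work. No visits or tests are added, and patient management does not change.

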### Patient and public involvement

We were keen to involve patients including those with Graves’ hyperthyroidism and their families in the design of this clinical trial. We therefore discussed the proposed trial with patients who had Graves’ hyperthyroidism within our clinical service and liaised with the Young Person’s Advisory Group (YPAG) in the North of England. We also discussed the trial with the BTF, and it was clear from these discussions that improving the treatment options for young people with this condition was an important area. YPAG and a representative from the BTF helped to refine the trial protocol and the patient information sheets. A member of the BTF was part of the trial steering committee, and the BTF published information regarding the trial on their website and facilitated recruitment by providing information to potential participants.

We intend to notify participants in writing regarding the trial outcome.

## Ethics and dissemination

Trial oversight consists of Trial Steering Committee (TSC), Data Monitoring Committee (DMC) and Trial Management Group (TMG). The TSC comprises an independent chair and three other independent members including a statistician. The DMC consists of three independent members, an endocrinologist (chair), immunologist and a statistician. The TMG will be responsible for overseeing the progress of the trial. The day-to-day management of the trial will be coordinated by the Newcastle Clinical Trials Unit, which will also be responsible for informing sites regarding protocol modifications and updates. Data management will be undertaken in accordance with the Newcastle University Clinical Trials Unit Standard Operating Procedures.

The results of this trial will be distributed widely at international endocrine meetings, including the European Society for Paediatric Endocrinology annual meeting. The results will be published in the peer-reviewed literature and distributed via patient support groups including the BTF.

## Discussion

Graves’ disease remains a challenge for young people and their families, with significant disadvantages associated with all standard treatment modalities. Most young people will ultimately be treated with thyroid hormone replacement which is not ideal from a practical, financial and quality of life perspective.^43^ The management of Graves’ hyperthyroidism is currently under review by National Institute for Health and Care Excellence.

This is a proof-of-concept trial that may be the precursor to a phase III trial. The limitations of the trial design include the need to adopt a largely pragmatic approach to the selection of the RTX dose and the fact that an impact on disease course may not be detected by a 2-year trial. On the other hand, patients who remit by 2 years may still be at risk of relapse at a later stage. There is also a risk that patients will experience side effects from ATD therapy which means this has to be stopped. If so, then definitive treatment may be required before the impact of RTX on the disease course can be elucidated. There is also a need to be cautious about assuming that remission rates following a course of ATD in a 12-year-old patient with Graves’ hyperthyroidism are similar to those in someone who is 20 years of age. Remission rate may therefore reflect the age of trial participants as well as the impact of the treatment regimen.

We feel that there are three disadvantages from the patient’s perspective when taking part in this trial. First, the infusion involves a day spent in hospital. The second disadvantage is the potential risk of adverse events, notably infections, although the literature does not suggest significant issues in an otherwise healthy and immune competent group of subjects like young patients with Graves’ hyperthyroidism who have received one or two doses of RTX. Finally there is the uncertainty about whether the intervention will impact on disease outcome favourably.

The number of clinic visits will be similar to patients with Graves’ managed routinely and will help to ensure that patients’ biochemistry is monitored carefully.

ATD does not cure young patients with Graves’ in the short term and is only associated with resolution of the hyperthyroid state in a minority of patients after several years of treatment. Surgery and RI remove or destroy the gland and hence are not a cure either. RTX provides the prospect of an earlier remission in patients with Graves’ hyperthyroidism who are therefore less likely to experience the side effects of ATD. RTX may cure patients who would otherwise not have been cured by ATD, and it may reduce the likelihood of long-term hypothyroidism. Repurposing RTX for this indication would mean an immediately translatable therapy with a well-established and favourable side effect profile, and a likely reduction in costs now that it is off-patent.

## Trial status

This manuscript is based on trial protocol V.4.0 dated 27 November 2017. The adjuvant rituximab, a potential treatment for the young patient with graves’ hyperthyroidism (RiGD) trial, opened to recruitment in October 2016 and is due to close to recruitment in October 2018.

10.1136/bmjopen-2018-024705.supp1Supplementary file 1

10.1136/bmjopen-2018-024705.supp2Supplementary file 2

10.1136/bmjopen-2018-024705.supp3Supplementary file 3

10.1136/bmjopen-2018-024705.supp4Supplementary file 4
